### 2.9. Blinding

A single-blind method will be used. Outcome assessors, data manager, and statistics analyzer will be blinded to group allocation. However, participants will not be blinded because each participant knows his or her group. Therefore, the results of the assessment will be kept confidential to the participants to improve the accuracy of the test indicators and assure the objectivity and reliability of the evaluation. Blinding will be maintained during the whole study process. After completion of the statistical analysis, the blind code will be disclosed.

## 3. Treatment

### 3.1. Basic Treatment

Based on their current medical history, all participants received routine treatment with essential drugs, including hypotension, hypoglycemia, antiplatelet aggregation, and lipid regulation.

### 3.2. Interventions

All participants (2 groups) will be given health education once a week understanding the management of risk factors such as hypertension, diabetes, hyperlipidemia, and obesity and the drug management of these diseases. In addition, participants in the EA group will receive electroacupuncture treatment five sessions a week. Participants will be intervened in screen-separated personal space and will not be allowed to communicate with each other. Treatment will be conducted within 8 consecutive weeks.

### 3.3. Control Group

The CG group will only receive health education without electroacupuncture treatment. After finishing this trial, electroacupuncture treatment can be freely provided if they need, which is the same as the EA group.

### 3.4. Electroacupuncture Group

Electroacupuncture treatment details are presented in Table 2 and are based on the revised Standards for Reporting Interventions in Clinical Trials of Acupuncture (STRICTA) 2010 checklist [24]. In the sitting position, wipe Baihui and Shenting with alcohol, then obliquely pierce the steel needle (Suzhou Medical Supplies Factory Co., Ltd., Jiangsu, China) with the 0.3 ∗ 25 mm into the skin of the head 0.5 inches deep, and then perform appropriate operations at each point (including lifting, thrusting, and rotating) for 10 seconds to achieve the needling sensation (De qi sensation). Finally, these two needles will be connected to a SDZ-II Huatuo Electroacupuncture Instrument (Hengshui Hengkang Medical Equipment Co., Ltd., Hebei, China) with electrode clamps for 30 minutes per day, 5 days per week, 8 consecutive weeks.

### 3.5. Outcome Assessment

All outcomes will be measured by several experienced assessors who have been trained to administer these assessments and are blinded to the randomization group after the baseline visit for evaluation. Meanwhile, ensure that each subject's pre- and postevaluations are conducted by the same assessor.

### 3.6. Primary Outcome

The primary outcome of this study is the changes in the score on MoCA from baseline to 8 weeks after intervention between the two groups and within groups. It is widely used for cognitive function assessment and can reflect the whole cognitive level of individuals. The MoCA has a maximum score of 30 points divided into eight parts, namely, visual space/executive ability (5 points), name (3 points), memory (5 points), attention (3 points), computing (3 points), language fluency (3 points), abstraction (2 points), and orientation (6 points). MoCA has excellent reliability and validity and is sensitive enough for clinical and research practice [25].

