### 2.2. Sample Size Calculation

In this procedure, the total score of the Montreal Cognitive Assessment Scale was invoked as the main effect index. The effect value was 0.9 in the treatment group and 0.725 in the control group [17], 0.8 in power and 0.05 in alpha. The sample size was estimated at PASS 24.0 software to be 116 cases, i.e., 58 cases in each group. Allowing 20% dropout rate, the total sample size was expected to be 140 patients (70 in each group).

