### 3.10. Statistical Analysis

IBM SPSS Statistics 24.0 software will be used to conduct the whole data analysis by an independent statistician who is unaware of group assignments. All continuous variables will be presented as mean ± standard deviation (SD), and categorical variables will be presented as numbers (%). The statistical significance level is considered to be 95% CIs (two-sided alpha *P* < 0.05).

The effect of the intervention will be assessed as the change in outcome measures between the baseline and eight weeks (after treatment sessions end), using a repeated-measures analysis of variance (ANOVA) and chi-square test.

The difference in effect between the CG group and the EA group will be assessed by comparing changes in the MoCA score and secondary outcomes including language learning and memory function, attention function, executive function, and visuospatial function using the independent *t*-test or Mann–Whitney *U* test on continuous variables and chi-square test or Fisher's exact test on categorical variables.

Intention-to-treat analyses will be used for all outcomes. A multiple imputation method will be carried out to fill in missing data for outcomes.

The structure and function of functional magnetic resonance will be analyzed by SPM software based on the MATLAB platform. Neural network analysis techniques such as VBM, ROI, and ICA will be used to compare the differences in functional connectivity changes between groups by independent sample *t*-test. FDR correction will be used for multiple comparison and correction.

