## Figures and Tables

**Figure 1 fig1:**
[figure not shown]
The planned flowchart of the trail. EA: electroacupuncture; HE: health education; MOCA: Montreal Cognitive Assessment; AVLT: Auditory Verbal Learning Test; TAP: Test of Attentional Performance; STROOP: Stroop color-naming condition; ROCFT: Rey–Osterrieth Complex Graphics Testing; rs-fMRI: resting-state functional MRI.

**Table 1 tab1:** The study schedule for enrollment, interventions, and assessments.

Items	Before enrollment −2 to −1 week	Intervention period 1–8 weeks	Outcome assessment 9 weeks
Inclusion criteria	×		
Exclusion criteria	×		
Informed consent	×		
Baseline	×		
Randomization and allocation	×		
Intervention		×	
Baker Depression Scale test	×		
MoCA	×		×
AVLT	×		×
TAP	×		×
STROOP	×		×
ROCFT	×		×
rs-fMRI	×		×
Adverse events		×	
Reasons of dropout and withdrawals		×	

**Table 2 tab2:** STRICTA checklist (details of intervention).

	Item	Detail
1. Acupuncture rationale	(1a) Style of acupuncture	Electroacupuncture based on traditional Chinese medicine theory
	(1b) Reasoning for treatment provided, based on historical context, literature sources, and/or consensus methods, with references where appropriate	Acupuncture points to be used in this study were Baihui (GV20) and Shenting (GV24) located at the head. Based on previous studies [21] and a large number of literature [22, 23], Baihui (GV20) and Shenting (GV24) will be mainly selected as acupuncture points for VCI treatment.
	(1c) Extent to which treatment was varied	Only EA group will receive electroacupuncture treatment

2. Details of needling	(2a) Number of needle insertions per subject per session	2
	(2b) Names of points used	Baihui (GV20) and Shenting (GV24)
	(2c) Depth of insertion, based on a specified unit of measurement	0.5 inches deep
	(2d) Response sought	“De qi” sensation
	(2e) Needle stimulation	Electroacupuncture
	(2f) Needle retention time	30 minutes
	(2g) Needle type	Sterilized stainless steel needle with the 0.3 ∗ 25 mm (Suzhou Medical Supplies Factory Co., Ltd., Jiangsu, China)

3. Treatment regimen	(3a) Number of treatment sessions	40 sessions (8 consecutive weeks)
	(3b) Frequency and duration of treatment sessions	30 minutes per day, 5 days per week

4. Other components of treatment	(4a) Details of other interventions administered to the acupuncture group	(a)All participants received routine treatment with essential drugs(b)All participants will be given health education once a week

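### The primary outcome counts within-group MoCA change alongside the between-group difference and does not rank them, so an uncontrolled before-after gain could be read as a positive primary result

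*Protocol article*

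**What the plan says.** Section 3.6 (Primary Outcome) defines the primary outcome as "changes in the score on MoCA from baseline to 8 weeks after intervention between the two groups and within groups". It gives no order of priority between the two contrasts.

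Section 3.10 (Statistical Analysis) has two relevant sentences. The first reads "The effect of the intervention will be assessed as the change in outcome measures between the baseline and eight weeks". It names a repeated-measures ANOVA and a chi-square test but no group-by-time term. The second reads "The difference in effect between the CG group and the EA group will be assessed by comparing changes in the MoCA score", together with the secondary outcomes, by independent t-test or Mann-Whitney U test. Neither is called the primary test.

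Section 2.2 (Sample Size Calculation) rests on a contrast between arms: "The effect value was 0.9 in the treatment group and 0.725 in the control group". It arrives at a sample size "to be 116 cases, i.e., 58 cases in each group", raised to 70 per group for 20% dropout.

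Table 1 shows one MoCA before treatment and one after it, the latter in the column headed "Outcome assessment 9 weeks".

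**The concern.** Only the between-group comparison is protected by randomisation. A before-after change in the EA arm combines any EA effect with everything else that moves MoCA over about nine weeks: practice from repeating the test, weekly health education, drug treatment of vascular risk factors, and possibly regression to the mean, because Section 2.5 selects patients on MoCA (18 to 26) and Table 1 shows a single pre-treatment MoCA. Sections 3.1 and 3.2 give the drugs and the education to both arms, so these influences are shared. They cancel in the between-group difference and remain in the within-group change.

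Because Section 3.6 makes the within-group change part of the primary outcome, an author who follows the text could report a significant rise in the EA arm as a positive primary finding even if the control arm rose equally. Section 3.10 makes this easier by calling the baseline-to-week-8 change the effect of the intervention and treating the group difference as a separate matter.

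**Working it through.** **1. Which contrast was sized.** Section 2.2 sets 0.9 against 0.725, with "0.8 in power and 0.05 in alpha". The scale is not stated, but the values behave as two proportions. With unpooled variance, n per group = [p1(1−p1) + p2(1−p2)] × (zα + zβ)² / (p1−p2)². Here the bracket is 0.090 + 0.199 = 0.289 and the squared difference is 0.175² = 0.0306. One-sided alpha gives 0.289 × (1.645 + 0.842)² / 0.0306 = 58.4, close to the stated 58. Two-sided alpha gives 74.2. That mismatch with the two-sided level in Section 3.10 is a separate matter. What counts here is that the calculation compares treatment with control, so the between-group contrast is the one that was sized.

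**2. No change in either arm.** Let A and B be the standardised mean changes in EA and control. The between-group statistic is (A − B)/√2, and each test is two-sided at 0.05. By simulation (2 million draws), the chance that the within-EA or the between-group test is significant is 8.3% (4.1% in EA's favour). For any of the three tests (within EA, within control, between) it is 11.5%.

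**3. No EA effect, but a gain shared by both arms.** Assumptions, since the article gives neither value: shared gain m = 0.5 to 1.5 points, SD of change s = 2 to 3 points. The number per arm is 70 × 0.8 = 56. For a paired t-test, the noncentrality is m/(s/√n) and the two-sided critical value is 2.004 on 55 degrees of freedom. Example: m = 0.5, s = 2.5 gives 0.5/(2.5/7.48) = 1.50 and a 31% chance of significance in EA's favour. Call that chance p. With no EA effect the arms are independent and alike, so significant in EA but not in control has probability p(1 − p).

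| Shared gain | SD 2: p; p(1−p) | SD 2.5: p; p(1−p) | SD 3: p; p(1−p) |
|---|---|---|---|
| 0.5 | 45%; 25% | 31%; 21% | 23%; 18% |
| 0.8 | 84%; 14% | 65%; 23% | 50%; 25% |
| 1.0 | 96%; 4% | 84%; 14% | 69%; 21% |
| 1.5 | nearly 100%; about 0% | 99%; 0.7% | 96%; 4% |

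Section 3.10 plans intention-to-treat with multiple imputation, so 70 per arm is also worth a look. There p is 28% to 54% at a gain of 0.5 and 79% to 98% at 1.0.

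The between-group test stays at 2.5% in EA's favour in every cell, because the shared gain cancels.

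**4. Regression to the mean as one source of shared gain.** With a normal source population truncated to 17.5–26.5 and reliability r, the expected drift is (1 − r) × (source mean − truncated mean). With SD 3 to 4 and r 0.7 to 0.9 (all assumed), a source mean of 25 gives +0.15 to +0.59 points, 23 gives +0.05 to +0.19, 22 gives 0, and 21 gives a negative drift. It may contribute, but the argument does not depend on it.

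**The case against.** The strongest reply is that the randomised comparison is already planned. The second sentence of Section 3.10 compares MoCA changes between arms, and Section 2.2 sizes a two-arm contrast. A fair reader would take that comparison as the intended primary test. This stands as mitigation. It does not rank the within-group part below the other, and no section says that within-group results are descriptive. A statistical analysis plan could repeat the definition in Section 3.6 or contradict it; either way the protocol's own wording needs correcting.

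A second reply is that Section 3.10 names no paired test within arms and no rule that significance in EA with non-significance in control counts as success. That is correct. The within-arm test used above is one way to carry out the within-group half of Section 3.6; the discordance rule is a possible misuse that a reader might infer, not a stated criterion. Its rate is p(1 − p), which cannot exceed 25% and falls to about zero when the shared gain is large, so it should not be quoted as a fixed error rate.

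A reader might also take the timing phrase in Section 3.6 to mean a visit at week 16. The article does not support this. The Abstract places assessment at 8 weeks of intervention, Section 3.10 ties week eight to the end of treatment sessions, the Discussion says there is no follow-up, and Table 1 has one post-treatment visit, at week 9.

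**Conclusion.** The point holds as a defect in the definition of the primary outcome: two contrasts share primary status without priority, and one of them cannot isolate the EA effect. With no EA effect, and on the stated assumptions (shared gain 0.5 to 1.5 points, SD of change 2 to 3, 56 per arm), a within-EA test would favour EA about 23% to nearly 100% of the time, against 2.5% for the between-group test. Significance in EA but not in control would occur about 0% to 25% of the time. These sizes depend on assumed values. What does not is the direction: any shared upward drift inflates the within-group result and leaves the between-group result untouched.

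The documents do not support the stronger readings that no between-group analysis is planned, or that the trial has adopted a before-after rule for success. The change should be made while the trial is still recruiting (Section 3.13) and before unblinding.

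**What to change.** In Section 3.6, remove the closing reference to within-group change. State that the sole primary comparison is the between-group difference in MoCA change from baseline to the single post-treatment visit in Table 1.

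In Section 3.10, define the effect of the intervention as that between-group difference. With two time points, the group-by-time term of the repeated-measures ANOVA and the equal-variance t-test on changes are the same test, so one can be named and the other dropped. Add that within-group changes are descriptive and cannot support the primary conclusion. Change from baseline remains the endpoint.

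The cost is wording in two sections. No visit, measurement or procedure changes, and this edit does not alter the sample size, because Section 2.2 already uses a treatment-versus-control contrast.

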### 3.7. Secondary Outcomes

Secondary outcomes include Auditory Verbal Learning Test (AVLT), Test of Attentional Performance (TAP), Stroop color-naming condition (STROOP), Rey–Osterrieth Complex Graphics Testing (ROCFT), and rs-fMRI, all of which will be evaluated at the same time points as the assessment of the primary outcome.

In this study, the AVLT will be used to evaluate language learning and memory function, which include three tests: immediate recall, short-term delayed recall, and long-term delayed recall [26].

Attention testing is accomplished by the TAP 2.3 attention testing system of PSYTEST Company to test attention span, duration, and functions mainly, which includes four test items: alertness, transfer attention, distracting attention, and response/nonresponse [27].

The STROOP compiled by prime psychological programming software consists of three parts: neutral test, consistency test, and reverse test. It mainly tests the executive function [28].

The visuospatial function was tested by ROCFT, which included the assessment of visual-spatial structure and visual memory [29].

Rs-fMRI will be performed using Philips Ingenia 3.0 T magnetic resonance imager. The data will be scanned by the Department of Radiology, General Hospital of Ningxia Medical University. The specific operation scheme is as follows.

### 3.8. Brain MRI Protocol

For participants, the imaging data which include conventional brain T1-weighted image (T1WI) and resting fMRI will be collected and acquired using a 3.0 T Ingenia scanner (Philips, the Netherlands) at the General Hospital of Ningxia Medical University. T1-weighted sequence and resting fMRI are shown as the following parameters, respectively [21].

T1: repetition time (TR) = 8.1 ms, echo time (TE) = 3.7 ms, flip angle (FA) = 8°, number of slices = 150, slice thickness = 1 mm, voxel size = 1 × 1 × 1 mm^3^, FOV = 240 mm ×240 mm, and matrix = 240 × 222.

Resting fMRI: TR = 2000 ms, TE = 30 ms, flip angle = 90°, number of slices = 36, slice thickness = 3.8 mm, voxel size = 3.01 × 3.09 × 3.80 mm^3^, FOV = 241 mm × 241 mm, matrix = 80 × 78, and phases per location = 240.

Participants will be requested to lie quietly in the scanner and close their eyes without thinking during the data acquisition process. Meanwhile, earplugs will be utilized to reduce the noise when the machine is running. Each scan lasted 1380 seconds.

### 3.9. Data Collection, Management, and Monitoring

Well-designed electronic CRF tables will be used for data collection. During the data collection process, a dependent research assistant (RA) will responsible for quality control. Two independent researchers will check the Case Report Form and Adverse Events Form carefully and input them into the computer to ensure data accuracy.

The project manager will have access to the data and be responsible for the initial data cleansing, identification, coding, and conversion to the appropriate data analysis format. All the original forms will be archived in the clinical research center of the General Hospital of Ningxia Medical University. Then, all data are treated with the utmost confidentiality and made anonymous to anyone outside the study.

The Data and Safety Monitoring Board (DSMB) of the clinical evaluation center of the General Hospital of Ningxia Medical University are responsible for data monitoring, i.e., obtaining any interim results and making the final decision to terminate the trial if any serious acupuncture-related EA occurs.

### 3.10. Statistical Analysis

IBM SPSS Statistics 24.0 software will be used to conduct the whole data analysis by an independent statistician who is unaware of group assignments. All continuous variables will be presented as mean ± standard deviation (SD), and categorical variables will be presented as numbers (%). The statistical significance level is considered to be 95% CIs (two-sided alpha *P* < 0.05).

The effect of the intervention will be assessed as the change in outcome measures between the baseline and eight weeks (after treatment sessions end), using a repeated-measures analysis of variance (ANOVA) and chi-square test.

The difference in effect between the CG group and the EA group will be assessed by comparing changes in the MoCA score and secondary outcomes including language learning and memory function, attention function, executive function, and visuospatial function using the independent *t*-test or Mann–Whitney *U* test on continuous variables and chi-square test or Fisher's exact test on categorical variables.

Intention-to-treat analyses will be used for all outcomes. A multiple imputation method will be carried out to fill in missing data for outcomes.

The structure and function of functional magnetic resonance will be analyzed by SPM software based on the MATLAB platform. Neural network analysis techniques such as VBM, ROI, and ICA will be used to compare the differences in functional connectivity changes between groups by independent sample *t*-test. FDR correction will be used for multiple comparison and correction.

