## Abstract

Vascular cognitive impairment no dementia (VCIND) is likely to develop into vascular dementia (VD) without intervention. The clinical efficacy of electroacupuncture (EA) for VCIND has been previously demonstrated. However, the neuroimaging mechanism of EA for VCIND has not been elucidated clearly. This trial is designed to provide solid evidence for the efficacy and neuroimaging mechanism of EA treatment for patients with VCIND. This ongoing study is an assessor-blind, parallel-group, randomized controlled trial. 140 eligible subjects will be recruited from the General Hospital of Ningxia Medical University and randomized into either the electroacupuncture (EA) group or the control group (CG). All subjects will receive basic treatment, and participants in the CG will receive health education performed weekly. Except for basic treatment and health education, participants in the EA group will receive treatment 5 times per week for a total of 40 sessions over 8 weeks. The primary outcome in this study is Montreal Cognitive Assessment (MoCA), and the secondary outcomes are Auditory Verbal Learning Test (AVLT), Stroop color-naming condition (STROOP), Rey–Osterrieth Complex Graphics Testing, and resting-state functional magnetic resonance imaging (rs-fMRI). All of the outcome measures will be assessed at baseline and 8 weeks of intervention. The medical abstraction of adverse events will be done at each visit. The results of this trial will demonstrate the efficacy and neuroimaging mechanism of EA treatment for VCIND, thus supporting EA treatment as an ideal choice for VCIND treatment. The trial was registered at the Chinese Clinical Trial Registry on 28 July 2018 (ChiCTR1800017398).

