### 2.5. Inclusion Criteria

Patients aged 50–75 years who (1) meet the diagnostic criteria of VCIND described above; (2) MoCA score of 18–26 [19, 20]; (3) are right-handed; (4) elapsed time after stroke ≥6 months; (5) have no acupuncture treatment in the last six months; and (6) volunteer to participate in the research and sign the informed consent were included in the study.

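### The MoCA comparison uses unadjusted change scores and names no single primary test; one baseline-adjusted ANCOVA would remove the ambiguity and add modest precision at no cost

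*Protocol article*

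**What the plan says.** Section 3.6 of the protocol article states: "The primary outcome of this study is the changes in the score on MoCA from baseline to 8 weeks after intervention". The contrast is to be made "between the two groups and within groups". There are two measurement times; the Abstract says "All of the outcome measures will be assessed at baseline and 8 weeks of intervention".

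Section 3.10 gives two analyses of change:

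- The effect of the intervention is assessed as change from baseline to eight weeks "using a repeated-measures analysis of variance (ANOVA) and chi-square test". No ANOVA term is named.
- "The difference in effect between the CG group and the EA group will be assessed by comparing changes in the MoCA score and secondary outcomes", with the "independent *t*-test or Mann–Whitney *U* test on continuous variables". No rule for choosing between them is given.

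The same section sets "two-sided alpha *P* < 0.05" and calls for intention-to-treat analysis with multiple imputation of missing outcomes. It does not rank the procedures, and none of them uses the baseline score as a covariate. Section 2.5 admits patients with a "MoCA score of 18–26".

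**The concern.** Two things are at stake.

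- **Which result is primary.** Three procedures are named for one outcome, with no order among them. Section 3.6 adds within-group change to the between-group contrast. A reader cannot tell which p-value and which interval will decide the trial.
- **Precision.** Baseline MoCA is scheduled for every participant and predicts the later score. Subtracting it forces a coefficient of 1 on baseline, whereas ANCOVA estimates that coefficient. When the true slope is below 1, the change score carries avoidable noise, and any chance baseline difference between the groups enters the result through regression to the mean.

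There is also a practical mismatch. Rubin's rules need an estimate and a standard error from each imputed data set. A Mann-Whitney p-value supplies neither directly, and the article names no way to pool it.

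**Working it through.** The plan has no figure of its own for this point. Section 2.2 gives 0.9 versus 0.725 without unit, SD or correlation, so the precision inputs below are assumptions and are shown as ranges.

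**1. How many different between-group tests are there?** With two visits, the group-by-time F of the repeated-measures ANOVA equals the squared t on change. A check on one simulated data set with 58 per group gave F = 9.8025 and t² = 9.8025, with p = 0.00221 for both. The three names therefore give two distinct between-group tests of change, t and Mann-Whitney.

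**2. Cost of leaving that choice open.** In 20,000 simulated null data sets (normal, 58 per group, r = 0.5), the type I error was 5.0% for the t-test, 5.0% for Mann-Whitney and 6.0% if the better of the two were taken.

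**3. Precision with equal variances.** Let σ be the SD at each visit and r the baseline to follow-up correlation.

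- Variance of change: 2(1−r)σ²
- Residual variance under ANCOVA: (1−r²)σ²
- Ratio, ANCOVA to change: (1+r)/2 = 0.65, 0.75, 0.85 for r = 0.3, 0.5, 0.7

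**4. Allowing for the entry window.** Table 1 lists one MoCA before enrolment, so the 18 to 26 criterion appears to act on the baseline value itself. Under a linear model, such selection leaves the slope (b = r) and the residual variance (1−r²)σ² unchanged but cuts the baseline variance to kσ². Then:

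- Variance of change: (1−r²)σ² + (1−r)²kσ²
- Ratio, ANCOVA to change: (1+r) / [(1+r) + (1−r)k]

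For a normal score centred at 22 (assumed) and cut at ±h, k = 1 − 2aφ(a)/[2Φ(a)−1], with a = h/σ. Here h = 4 for a cut at 18 and 26, and h = 4.5 if scores are treated as rounded to whole points.

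| Unselected SD | h | k | Saving, r = 0.3 | r = 0.5 | r = 0.7 |
|---|---|---|---|---|---|
| 2.5 | 4.5 | 0.694 | 27% | 19% | 11% |
| 2.5 | 4 | 0.601 | 24% | 17% | 10% |
| 3 | 4 | 0.465 | 20% | 13% | 8% |
| 4 | 4 | 0.291 | 14% | 9% | 5% |
| 5 | 4 | 0.196 | 10% | 6% | 3% |

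One cell in full, for SD 2.5, h = 4.5, r = 0.3: 1.3 / (1.3 + 0.7 × 0.694) = 1.3/1.786 = 0.728, a saving of 27%.

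**5. Power.** Take 56 per group (70 less 20%), two-sided 0.05, and an assumed difference of 0.525 SD of change. This is close to the 0.52 that 58 per group would detect with 80% power, but the article does not state it. Noncentral-t power of the change-score test is 78.6%. Dividing 0.525 by the square root of the ratio gives:

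- ratio 0.728: 89.7%
- ratio 0.866 (SD 3, r = 0.5): 84.1%
- ratio 0.967 (SD 5, r = 0.7): 80.0%

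**6. Chance imbalance.** If the groups differ by D points at baseline, the change-score contrast shifts by −(1−b)D. With D = 0.5 and b = 0.5, both for illustration, that is −(0.5 × 0.5) = −0.25 points.

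**The case against.** The strongest reply is that the planned comparison is already valid. Allocation is randomised, so the difference in mean change is unbiased and the t-test holds its level; an article may also leave a rule for t-test versus Mann-Whitney to the analysis plan. The first part stands, which makes this a point about efficiency and clarity, not about a wrong test. The second part stands only for the choice rule: the article itself fixes the comparison of unadjusted changes and lists its procedures without rank.

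Several stronger readings are tempting, and the documents do not support them:

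- **The narrow entry window makes change scores lose most.** The window does lower r, but it also shrinks baseline variance, which is the source of the change score's extra noise. On the model above the gain becomes smaller. The equal-variance savings of 15% to 35% would be too large for MoCA.
- **Three tests compete.** Only two distinct between-group tests of change exist. The simulated type I error reaches 10.9% only if the ANOVA group main effect is also allowed to count as the result, and the article does not say that it would.
- **The test will be picked after seeing the data.** Section 3.10 is silent on this.
- **Mann-Whitney cannot be pooled.** It can be, through an associated estimate such as the probability of superiority with its standard error. It is just not direct.
- **Change scores are biased.** They are distorted only conditional on a chance imbalance.

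**Conclusion.** The point holds as a recommendation worth acting on. The article specifies an unadjusted change-score comparison and leaves open which procedure gives the primary MoCA result. ANCOVA on baseline would give one estimate with one interval, would protect against chance imbalance, and would reduce variance by roughly 3% to 27%, taking power at 56 per group from 79% to about 80% to 90%.

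The size rests on assumptions that are not in the documents: an unselected SD of 2.5 to 5 points, equal unselected variances at the two visits, r of 0.3 to 0.7, a linear relation, scores centred at 22, selection on the baseline MoCA itself, and a difference of 0.525 SD of change. The direction is more secure: in large samples, linear adjustment for baseline is at least as precise as the change score. At the low end of the range the gain in power is slight, and the main benefit is then a single unambiguous primary analysis.

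**What to change.** In section 3.10, name one primary analysis: ANCOVA (linear regression) of 8-week MoCA on group and baseline MoCA, two-sided 0.05, fitted in each imputed data set, pooled by Rubin's rules and reported as an adjusted mean difference with 95% CI. In section 3.6, make the between-group contrast the primary one and treat within-group change as descriptive.

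Use the same model, each outcome with its own baseline, for the continuous cognitive secondary outcomes (AVLT, TAP, Stroop, ROCFT). Keep Mann-Whitney on change as a sensitivity analysis and drop the repeated-measures ANOVA.

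The cost is analysis wording only, since the baseline measurements are already scheduled. Section 3.13 reports that recruitment and intervention are ongoing, and section 2.9 keeps the allocation code closed until the analysis is complete, so the change can still be prespecified.
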